**Intervention A**: PROMs data collection by follow-up data collectors over the **telephone**
An attempt to contact patients via phone will be made up until 21 days post diagnosis/treatment. Each day a data collector will make one attempt to contact the patient.Patients responding will have PROMS entered directly to the PCOR-VIC web system.Patients will be considered lost to follow up if they do not respond after 21 days from 12 month “Anniversary Date”.

**Intervention B**: Data collection by follow up data collectors by **mail (postal service)**
The EPIC-26 survey will be mailed to patients if they are contacted any time from 21 days before, up to and including the “Anniversary Date”. The survey will be accompanied with a personalised, signed letter with instructions and a postage-paid, self-addressed envelope.If the survey is not returned by 14 days post the Anniversary Date, patients will be telephoned as per Intervention A. Data collector will make one attempt each day i.e 14 attempts in total.Patients will be considered lost to follow up if they do not respond after 21 days from 12 month “Anniversary Date”.

**Intervention C**: Data collection by **E-mail** link to online surveyIf email is not available then the participants will be randomly assigned to either telephone (intervention A) or mail (Intervention B).A Uniform Resource Locator (URL) which is the address of a web page link to the EPIC-26 survey will be emailed to participants if they are contacted any time from 21 days before, up to and including the “Anniversary Date”.If participants do not complete the online survey by 14 days post the Anniversary Date, patients will be telephoned as per Intervention A. Data collector will make one attempt each day i.e 14 attempts in total. Patients will be considered lost to follow-up if they do not respond after 21 days from 12 month “Anniversary Date”.

## Duration of the project

We anticipate that the recruitment process will commence on the 1^st^of February 2016. Data collection will take place between February 2016 and November 2016. Based on current number of patients that become eligible for follow-up each month, we anticipated that it will require approximately 8-9 months to reach our total sample size of 687. An additional 2 months will be required for entering, analysing costing data and for report writing and developing draft manuscripts.

## Data collection, quality and monitoring methods

We will employ quantitative methods of data collection through structured questionnaires. For costing, the ABC [33] method will be adopted. Table 2 describes the data collection methods that will be used to obtain data for each specific objectives. Data will be collected by trained data collectors and supervised by the project manager and study investigators. Data collectors are from an academic institution (Monash University) and are independent of the hospitals. To ensure data quality, validation tools will be built in the web-based system. Routine monitoring meeting will also be held to ensure any problems encountered during data collection and randomization process.

**Table 2 Tab2:** Description of the specific objectives and methods

	Objectives	Methods
1	To compare the completeness of data across the three data collection approaches.	Total number of completed surveys will be identified in and compared across each of the three PROMS data collection approaches. Both the paper and electronic version provide capacity for patients to decline to answer any question. Provision in the electronic survey exists to alert patients where fields are left blank to prevent missing data issues.
2	To measure the cost of data collection of three different methods: Telephone, Mail (Postal services) and Email for Patient Reported Outcome Measures (PROMs) data in PROC-Vic.	The Activity Based Costing (ABC) method will be followed to estimate the cost of the operational activities of the three different methods of follow up. The costing data will be collected from provider perspective. Table 3: Describes the itemized costs of the 3 different methods.
3	To compare the cost and effectiveness of three different methods of data collection	Cost-effectiveness: Total cost (Personnel, recurrent, supply---)/Number of completed follow-up patients
4	To develop a model to determine the cost for national scale-up of PROMs data collection method with EPIC-26 survey in Australia.	A cost projection model will be developed based on most efficient approach. The model will use epidemiological data and estimated cost parameters. Estimated incidence data on national prostate cancer cases and completed follow up of patients will be forecasted. Using estimated cost data will help to determine the cost for national scale-up of follow up per year. A sensitivity analysis will be conducted with different assumptions e.g. (1) total number of prostate cancer patients; (2) completed follow up surveys and; (3) cost.
5	To provide recommendations for most cost-effective approach for complete follow-up of prostate cancer patient	A comprehensive report with recommendations will be developed.

## Data analysis plan

### Primary and secondary outcomes

For the primary outcome measure (completeness of surveys), we will estimate individual proportions with 95% CI for each arm of the trial. We will then calculate the pooled sample proportions for each pair and the standard error of the difference. Using these measures, we will calculate the Z score test statistics. The p value will be reported for the difference and P < 0.05 will be considered as statistically significant.

For the secondary outcome measures, we will carry out independent sample t-tests to detect the difference.

Analysis will be conducted by intention to treat (ITT) [39] as well as per protocol method [40]. The ITT method will allow us to evaluate the effect of each intervention in a real life situation (i.e. when subjects are randomized to the ‘email group’ but end up in the ‘telephone’ or ‘mail’ methods instead). The per-protocol method will allow us to study the direct effect of each option.

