## Sample size

Sample size calculations were based on an equivalence study design [35] and the primary outcome measure (completeness of survey responses). Given the current follow up response rates from the PCOR-VIC we estimate that we will achieve a response rate of 90% [32] when PROMs are administered by the telephone follow-up method. The study was designed to evaluate whether the completeness of survey responses in the ‘mail/postal service group’ or ‘email group’ was similar to the ‘telephone’ group. Assuming that the equivalence margin is 10%, we will require 190 respondents per group. We have made an assumption that the 83% of who have internet access will also have an email account [36]. The sample size was adjusted accordingly so the final number of respondents required in each group is 229 giving a total number required n = 687 (Table 1). Our sample size has been calculated to provide a level of significance at 5% with 80% power (2-sided test). The sample size calculation was performed in Stata V13.0 [37].

**Table 1 Tab1:** Sample size calculation

Indicator	Targeted response rate	Equivalence margin	Sample size (SS) per group	Internet access	SS adjusted for email	Total Sample required
Response rate	90%	10%	190	83%	229	687

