## Discussion

Through this economic analysis we will determine the most cost-effective means of capturing PROMs and completing follow up of prostate cancer patients through the PCOR-VIC using the EPIC-26 survey. Our primary aim therefore is to identify the value of different PROMS collection methods. Value is defined as outcomes relative to costs and encompasses efficiency [43]. The outcome we will be evaluating is response rates and representativeness of the various tools in assessing the quality of life. With knowledge of the cost of each completed survey, we will decide which approach to use as we expand data collection to obtain national coverage. Our primary objective is to assess the response rate across each data collection approach. Surveys will only be considered as completed if all relevant questions have been answered.

This will provide guidance to other registries undertaking follow up surveys of patients and it will also allow us to estimate the cost for collecting PROMs data within the Prostate Cancer Outcome Registry- Australia. Moreover we will be able to understand the quality of PROMs data collected by the three different methods. It may be that one method produces significantly higher rate of missing data or questions which patients decline to answer. We have to weigh the cost of data collection against completeness of surveys to determine the method which provides the greatest value at the end of the study. This decision will be made by the project steering committee and the funder.

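### The trial is sized for two comparisons with telephone, but the primary analysis tests all three pairs for a difference at P < 0.05 each, giving about a 12% chance of at least one false mode difference when completion is equal

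*Protocol article*

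**What the plan says.** The Sample size section treats telephone as the reference. It asks whether "completeness of survey responses in the ‘mail/postal service group’ or ‘email group’ was similar to the ‘telephone’ group", which is two contrasts. It assumes 90% completion, a 10-point equivalence margin, a two-sided 5% level and 80% power, and arrives at 190 per group, or 229 after allowing for email access (687 in total).

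The Data analysis plan (Primary and secondary outcomes) gives each arm's proportion with a 95% CI and then says: "We will then calculate the pooled sample proportions for each pair and the standard error of the difference". A Z statistic follows for each pair, and "The p value will be reported for the difference and P < 0.05 will be considered as statistically significant". With telephone, mail and email there are three pairs. The section ranks none of them above the others and gives no testing order, overall test or division of the 5%.

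**The concern.** The set of comparisons used for sizing is not the set that will be tested. Two contrasts with a common reference have become three contrasts of equal standing, each with its own 5% chance of a false positive. A reader of the results would not know which contrast answers the primary objective. Pairwise results can also disagree: email may differ from telephone while mail does not differ from either. The plan does not say how such a pattern is to be reported. What is at stake is the reliability of a statement in the main report that one mode yields more or fewer complete surveys than another.

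**Working it through.** **Inputs.** From Sample size: completion 90%, margin 0.10, 5% two-sided, power 80%, 190 per group, 83% internet access, 229 per group, 687 in total. From Randomisation process: blocks of 3 and 6, so equal allocation is taken. From Data analysis plan: pooled z-test for each pair, P < 0.05.

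**1. Reproduce the plan's figure.** For equivalence with equal true rates p, n = 2p(1 − p)(z_α + z_β/2)² / margin².
- At 2.5% per side: 2 × 0.9 × 0.1 × (1.960 + 1.282)² / 0.10² = 189.1, so 190. This matches.
- At 5% per side: 154.1, so 155. This does not match.
- 190 / 0.83 = 228.9, so 229, and 3 × 229 = 687. Both match.

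The design is therefore a single pairwise equivalence comparison at 2.5% per side. It contains no allowance for several contrasts.

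**2. Error of the difference tests as written.** Assume the three true rates are equal. The three z statistics share arms and are correlated. The chance that the largest pairwise |z| exceeds 1.96 comes from the studentized range with k = 3: P(Q > 1.96 × √2) = 12.2%. For comparison, three independent tests would give 1 − 0.95³ = 14.3%, and the simple sum is 15%.

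Simulation of the pooled z-test at true rates of 85% or 90% and 190 or 229 per arm gives:

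| Tests read at P < 0.05 | Chance of at least one false difference |
|---|---|
| One pair | about 5.0% |
| The two telephone pairs | about 9.0–9.2% |
| All three pairs | about 12.1–12.3% |

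Extending to a 95% rate and to an unequal split of 249/248/190 leaves the three-pair figure between 11.7% and 12.3%.

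**3. The same question under the equivalence rule.** Here the error is declaring equivalence when the true difference is at the margin. Take telephone 90% with mail and email both 80%. Declare equivalence when the 95% CI of the difference (unpooled standard error) lies inside ±10 points.
- 190 per arm: 2.6% per contrast, 5.0% for at least one of the two.
- 229 per arm: 2.7% per contrast, 5.1% for at least one of the two.

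With 2.5% per side, two contrasts can add to no more than a nominal 5%. The small excess over 2.5% per contrast comes from the normal approximation.

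**4. Check of the overall test as a gate.** If pairwise P values are read only when the 3x2 chi-square test is significant at 5%, the chance of any false difference under equal rates is 4.9–5.0%. With three arms, any two equal pairs imply that the third is equal too. The only true-null situations are therefore all arms equal, which the chi-square test holds at 5%, or exactly one pair equal, which its own 5% test controls.

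**The case against.** Several objections have force.

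- *The protocol never promises 5% across the set.* This stands. Both sections use 5% per test. A reader might infer that a claimed overall error rate is breached, but the text makes no such claim. The point is only that the per-test level does not extend to three tests.
- *This is an equivalence trial, and on that question the inflation largely disappears.* This also stands. A reader might carry the 12% over to equivalence conclusions, but step 3 shows about 5% for the two telephone contrasts. The inflation belongs to the difference tests that the analysis section actually prescribes. That those tests never use the margin is a separate weakness, which an adjustment of alpha would not cure.
- *No pairwise P value chooses the mode.* This stands. A reader might infer a 12% risk of adopting the wrong mode. The Economic analysis section defines the preferred approach by completion and cost, and the Discussion leaves the decision to the steering committee and the funder. The Discussion remark "It may be that one method produces significantly higher rate of missing data or questions which patients decline to answer" speculates about results and sets no test rule.
- *The primary objective compares all three approaches, so testing every pair is natural, and ranking of contrasts may be left to a SAP.* This stands in part. Comparing all pairs is a legitimate aim, but the Sample size section frames the question against telephone. The protocol also does not leave the matter open: it fixes both the pairs and the threshold.

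**Conclusion.** The mismatch is real and worth correcting. As written, the primary analysis has about a 12% chance of reporting at least one false difference between modes, or about 9% if only the telephone pairs are read, against 5% for a single pair. The figure assumes equal true completion in all three arms and hardly moves with the rate, the group size or moderate imbalance. It counts false differences in completion only. It leaves out any further looks from running both intention-to-treat and per-protocol analyses. It does not measure the error of an equivalence claim or the risk of choosing a mode wrongly, and the documents support neither of those readings. Dropping mail versus email is not enough while difference tests remain, since about 9% is left.

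**What to change.** In the Data analysis plan, Primary and secondary outcomes:

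1. Name mail versus telephone and email versus telephone, by assigned arm, as the two confirmatory contrasts. Judge each by the 95% CI of the difference in completion against the 10-point margin already set in the Sample size section.
2. Make mail versus email supportive.
3. If the pairwise P < 0.05 difference tests are kept, read them only after a significant overall 3x2 chi-square test at 5%.

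The cost is a few sentences and, if the P values are kept, one extra test. The sample size is unchanged, because the 95% CI rule uses the same 2.5% per side that yields 190 per group. The downside is that an isolated pairwise P just under 0.05 without a significant overall test can no longer be claimed as a finding.

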### Trial design

The study design proposed for this evaluation is an equivalence RCT design. Participants will be individually randomized to one of three independent groups receiving the PROMs instrument by email, post or by telephone. Due to the nature of the intervention, it is not possible to blind the researchers or study participants.

To collect costing data we will use an Activity Based Costing (ABC) method [33] and structured questionnaires to estimate the cost of the operational activities of the three different methods of follow up. The ABC method is useful for understanding key activities of any programs and interventions and allows identification of (i) implementation levels and composition of costs; (ii) variations in how an intervention is implemented over time and associated cost implications; and (iii) resulting costs of increasing coverage of cost-effective data collection methods. This method is flexible, so its resulting estimates can be easily understood and adapted to measure the cost of data collection of the three different methods. Costs that will be considered include personnel cost, cost of supplies (e.g., envelopes, printing etc.), cost of training of data collectors and cost of operation and maintenance (e.g., telephone bill, internet bill, rent etc.) for each of the data collection methods.

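### The trial is designed and sized to show equivalence within 10 points, but its primary analysis is a z-test for a difference that never uses the margin

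*Protocol article*

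**What the plan says.** Under Trial design the Protocol article states: "The study design proposed for this evaluation is an equivalence RCT design". The Abstract and Background describe the trial in the same way. The Sample size section sets the aim as finding out whether mail or email matches telephone on completeness, and gives the basis: "Assuming that the equivalence margin is 10%, we will require 190 respondents per group". It expects 90% completion by telephone, uses a two-sided 5% level and 80% power, and divides by 83% for email access to reach 229 per group and 687 in total.

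Under Data analysis plan, Primary and secondary outcomes, each arm's proportion gets its own 95% confidence interval. Then: "We will then calculate the pooled sample proportions for each pair and the standard error of the difference". A Z statistic follows, and the reading rule is: "The p value will be reported for the difference and P < 0.05 will be considered as statistically significant". The 10% margin appears in the Sample size section and Table 1, and nowhere in the analysis section.

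**The concern.** An equivalence trial takes as its null hypothesis that the arms differ by at least the margin, and it claims equivalence when the data rule that out. The stated analysis has the hypotheses the other way round: its null is that the arms are equal. Failing to reject that null does not show that the difference is small. Rejecting it does not show that the difference is large enough to matter.

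The pooled standard error assumes equal proportions, so the Z statistic cannot be reinterpreted as a test against the margin. The per-arm intervals do not bound the difference either. Running the same test in both the intention-to-treat and per-protocol populations does not change what it tests.

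Completeness is the primary outcome and one side of the cost-effectiveness comparison that is meant to inform national expansion. A claim that mail or email performs as well as telephone would rest on a test that is easier to pass the smaller the trial is.

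**Working it through.** **Inputs (Protocol article).** Completion 90%, margin 10 points, two-sided 5%, power 80%, 190 then 229 per group, email access 83% (Sample size, Table 1). Current registry response 85% (Background). Pooled z-test at P < 0.05 (Data analysis plan). I take the margin as absolute and symmetric, ±10 points.

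**Step 1: reproduce the sample size.** For equivalence of two proportions with a true difference of zero:

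n = 2p(1−p)(z₁₋α + z₁₋β/₂)² / margin², where α is the error per side.

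- 2.5% per side (two-sided 95% interval): 2 × 0.9 × 0.1 × (1.960 + 1.2816)² / 0.10² = 189.1, so 190. This matches.
- 5% per side (90% interval): 154.1, so 155. No match.
- Superiority test of 90% v 80%, two-sided: 199. No match.
- 190 / 0.83 = 228.9, so 229; 229 × 3 = 687. Both match.

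The plan was therefore sized for a 95% interval for the difference lying wholly within ±10 points. Its 80% power is the chance of that event when both arms are truly at 90%.

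**Step 2: compare the two rules.** With a and b the observed proportions and p̄ their mean:

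- z-test: |b − a| / √(2p̄(1−p̄)/n) > 1.96 is significant.
- Interval rule: (b − a) ± 1.96 √([a(1−a) + b(1−b)]/n) must lie inside ±0.10.

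Exact binomial enumeration gives:

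| True rates | n per group | z-test non-significant | Interval rule declares equivalence | Significant, yet interval inside ±10 |
|---|---|---|---|---|
| 90% v 80% | 190 | 21.2% | 2.7% | 0.0% |
| 90% v 80% | 229 | 14.2% | 2.7% | 0.0% |
| 85% v 75% | 190 | 31.1% | 2.4% | 0.0% |
| 85% v 75% | 229 | 23.3% | 2.5% | 0.0% |
| 90% v 90% | 190 | 95.0% | 80.0% | 0.01% |
| 90% v 90% | 229 | 95.0% | 88.9% | 0.08% |
| 97% v 93% | 190 | 56.6% | 76.0% | 19.7% |
| 97% v 93% | 229 | 49.5% | 83.2% | 33.7% |

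In the first four rows the true difference equals the margin, so any claim of equivalence is wrong. If only 100 per group were analysed at 90% v 80%, the z-test would be non-significant in 48.2% of trials and the interval rule would claim equivalence in 1.3%. Less data makes the z-test look more favourable, which is the reverse of what an equivalence analysis should do.

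**Step 3: two data sets at 229 per group.**

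- 206/229 (90.0%) v 193/229 (84.3%): z = −1.81, p = 0.070, not significant. The 95% interval for the difference is −11.8 to +0.4 points, so equivalence is not shown.
- 222/229 (96.9%) v 211/229 (92.1%): z = −2.26, p = 0.024, significant. The 95% interval is −8.9 to −0.7 points, so equivalence is shown.

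In each case the p value points away from the answer that the margin gives.

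**The case against.** The strongest reply is that the article never says a non-significant result means similar. It only attaches the label significant to P < 0.05. That is correct, and the error rates above are conditional on that reading. But the section offers no other way to reach a conclusion of similarity, so without that reading the primary analysis leaves the design question unanswered.

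Second, the significant-yet-equivalent case needs high completion. At a true 90% v 90% it occurs in under 0.1% of trials, and at 90% v 86% or 85% v 81% it is 0.0%. Nor is it false to call 97% and 93% different. This stands: that direction matters only if completion is well above the planned rate, and the harm lies in reading different as not equivalent.

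Third, the choice of mode will be made on cost-effectiveness ratios and by the steering committee and funder, not on this p value. That limits the consequence for the choice but does not rescue the primary equivalence claim.

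Fourth, an article may leave an interval for the difference, and the method for computing it, to a fuller document. Agreed. The criticism is not that detail is missing but that the article names a test, a variance and a threshold that do not fit its own design.

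**Conclusion.** The concern holds and must be fixed. The design and sample size call for a margin-based equivalence analysis, and the stated primary analysis is a test of no difference. The 80% power describes an analysis that is not planned.

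With non-significance read as similarity, a mode exactly at the margin would pass in 14.2% to 21.2% of trials at 90% v 80%, and in 23.3% to 31.1% at 85% v 75%, against 2.4% to 2.7% under the interval rule. These figures assume an absolute, symmetric margin, independent responses and a simple unpooled (Wald) interval. The central contradiction depends on none of these assumptions. The sample size arithmetic itself is correct.

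**What to change.** Replace the z-test as the decision rule in Data analysis plan, Primary and secondary outcomes. Suggested content:

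- For mail v telephone and for email v telephone, report the difference in completion proportions with a two-sided 95% confidence interval (unpooled, Newcombe or Miettinen–Nurminen; name one in advance).
- Conclude equivalence only if the whole interval lies between −10 and +10 percentage points.
- Keep the p value for a difference as descriptive and say that it does not decide equivalence. The sample size section sets both new modes against telephone, so mail v email can also be descriptive; if the team wants an equivalence claim there too, the same interval rule should apply.

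The 95% level should be kept, because it is the level that yields 190 per group.

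The cost is wording only: no new data, and no more patients under the plan's own assumption of 90%. One condition should be acknowledged. If true completion is 85% in both arms, the current rate given in the Background, power under this rule is 56% at 190 per group and 70% at 229. That follows from the completion rate assumed in the sizing, and keeping the z-test would not cure it.
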